### Participants

Four German university hospitals are participating in the study: Frankfurt, Bonn, Kiel, Muenster. The PBM program includes all patients undergoing surgical procedures ranging anywhere from: orthopaedic and visceral surgery, general surgery, cardiothoracic surgery, trauma, otorhinolaryngology, gynecology and obstetrics, urology, oral and maxillofacial surgery, vascular surgery, and neurosurgery to increase applicability of the evidence obtained during this trial. Exclusion criteria are: <18 years, ophthalmologic or dermatologic or outpatient surgery. If a patient has multiple hospital admissions during the study period, the first hospital stay will be analysed.

The control group will be composed of the patients treated according to the standard protocol in charge before implementation of the PBM program. A period of three months was allowed for the implementation of the PBM components. Patients treated after implementation will be allocated to the PBM cohort until July 2015.

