### Management

For consistent implementation regular teaching sessions were held at the beginning of the program and are repeated every six months. The focus is on clinical practice, outcome and safety issues in order to increase knowledge on PBM and awareness of the clinical implications of anaemia and the need for alternatives to transfusion. The new program is additionally promoted through hand outs, posters, checklists and web-based information among health care providers and patients.

Our PBM program has three main pillars:**Preoperative optimisation of haemoglobin levels:**

The preoperative detection, evaluation and therapy of anaemia diagnosis and treatment focuses specifically on those patients (aged 18 years and older) scheduled for elective surgery. Figure 1 shows the work-flow used at the University Hospital Frankfurt. Surgeries associated with a risk for transfusion >10% were identified by retrospective analysis of hospital data from 2011 with the hospital-information system Agfa ORBIS. Patients scheduled for elective surgery falling in that spectrum are screened and treated at the earliest possibility according to NATA and SABM recommendations if surgery can be postponed for at least four days (Figure 1) [12]. Iron deficiency anaemia (IDA) is treated with intravenous iron. Anaemic patients are suggested to be scheduled for both haematological and/or gastroenterological consultations for further diagnostics and optimal treatment of anaemia in cases where iron deficiency anaemia is unlikely.

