### Statistical analysis

The primary aim is to prove non-inferiority of the intervention (PBM) cohort when compared with the control cohort stratified by center. The primary composite endpoint will be registered electronically by analysis of ICD-10 diagnoses and will be exported to a data base. It will be analysed with a one-sided Mantel-Haenszel test with significance level of α =2.5% for the odds ratio resulting in H0: OR ≥ OR* vs. H1 OR < OR* with OR* being derived from the incidence in the control cohort and an incidence rate of the PBM cohort which is increased by the non-inferiority margin of 0.5%. As secondary analysis, we will analyse two-sided 95% confidence interval for the difference in the frequency of the composite safety endpoint as well as for the odds ratios and the single components of the composite endpoint. Additionally, the influence of covariates, e.g. the calendar year, concomitant diseases, the asynchrony of the study periods at different sites will be assessed statistically. Should there be a significant influence on the incidence of the composite endpoint, the Mantel-Haenszel test will be supplemented with a respective multivariate approach accounting for covariates.

Secondary endpoints will be compared with a two-sided Wilcoxon-Mann–Whitney test using a significance level of α =5%. A subgroup analysis will assess if there is some bias from not excluding patients with multiple hospital stays for surgical intervention during the study period. A further subgroup analysis will assess if there is a difference of safety between a) elective patients who will receive preoperative haemoglobin optimisation compared to b) anemic patients who will not undergo preoperative haemoglobin optimisation due to failed postponement of surgery in case of surgical urgency or non-elective surgery, respectively.

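### The subgroup analysis of preoperative optimisation confounds it with surgical urgency, so it cannot show whether optimisation, or the delay it needs, is safe

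*Protocol article*

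**What the plan says.** The last sentence of the Statistical analysis section of the protocol article sets out the analysis: "A further subgroup analysis will assess if there is a difference of safety between" two groups, namely "elective patients who will receive preoperative haemoglobin optimisation compared to b) anemic patients who will not undergo preoperative haemoglobin optimisation". It gives the reason why the second group was not optimised: "due to failed postponement of surgery in case of surgical urgency or non-elective surgery, respectively".

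The Management section says who can be optimised. The pillar "focuses specifically on those patients (aged 18 years and older) scheduled for elective surgery". Within that population, screening and treatment apply to operations identified as carrying a transfusion risk above 10%, and only "if surgery can be postponed for at least four days".

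The Participants section defines the comparison cohort of the trial: "The control group will be composed of the patients treated according to the standard protocol in charge before implementation of the PBM program". The primary analysis names that cohort, since it concerns "non-inferiority of the intervention (PBM) cohort when compared with the control cohort stratified by center". The subgroup sentence does not mention it.

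**The concern.** The two groups differ in whether they were optimised, but also in whether surgery could wait, and the second difference is what produces the first. Patients whose surgery cannot wait may have a different risk of infarction, stroke, renal failure, pneumonia, sepsis or death whatever is done about their haemoglobin. A difference between the groups, or the lack of one, would then say nothing definite about optimisation.

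The Discussion of the article names delay of surgery for preoperative optimisation as one of the two main safety worries about PBM. The subgroup comparison is the only analysis the article describes that is directed at optimisation. If it is reported as written, a reader could take it as evidence on that worry, which it cannot provide.

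**Working it through.** The plan gives no effect size, group size or test for this analysis, so there is no figure to reproduce. The check has three steps.

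**1. The definitions side by side**

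| | Group (a) | Group (b) |
|---|---|---|
| Optimised | yes | no |
| Surgery could wait | yes (elective, at least four days) | no (urgent, non-elective or postponement failed) |
| Limited to transfusion risk above 10% | yes, through the Management section | no limit stated |
| Cohort, read literally | PBM | PBM |

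The first two rows always move together. By definition (a) contains nobody whose surgery could not wait, and (b) contains nobody who was optimised. With no overlap, adding urgency to a regression model cannot separate the two effects. The third row adds a partial imbalance in type of procedure. The fourth follows because the groups are identified by receipt of a PBM component, or by failure to postpone for it, and control patients were treated before that component was introduced.

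**2. What the contrast estimates**

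On the odds-ratio scale, and assuming multiplicative effects,

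observed OR (a versus b) = optimisation OR ÷ urgency OR (b versus a).

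- Optimisation harmful at 1.2, urgency 1.5: 1.2 / 1.5 = 0.80.
- Optimisation protective at 0.8, no urgency effect: 0.8 / 1.0 = 0.80.
- Optimisation harmful at 1.5, urgency 1.5: 1.5 / 1.5 = 1.00.

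An observed 0.80 is thus compatible with harm and with benefit, and an observed 1.00 does not exclude harm. If the net baseline odds ratio of (b) against (a) were below 1, the distortion would run the other way.

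**3. Illustration of size, under assumptions**

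Assume that optimisation has no effect. Take an event rate of 10% in (a), the overall incidence given under Sample size and power calculation. The urgency odds ratios and the group size of 1,000 are assumptions and are not in the documents.

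Rate in (b) = odds / (1 + odds), where odds = (0.10 / 0.90) × urgency OR. For an OR of 1.5: 0.1111 × 1.5 = 0.1667, and 0.1667 / 1.1667 = 14.3%.

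The chance of a two-sided 5% significant difference is approximately Φ(difference / SE − 1.96). For an OR of 1.5: SE = √(0.10 × 0.90 / 1000 + 0.143 × 0.857 / 1000) = 0.0146, 0.0429 / 0.0146 − 1.96 = 0.98, and Φ(0.98) = 84%.

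| Assumed urgency OR | Rate in (b) | Difference, points | Chance of significance, 1,000 per group |
|---|---|---|---|
| 1.25 | 12.2% | 2.2 | 35% |
| 1.5 | 14.3% | 4.3 | 84% |
| 2 | 18.2% | 8.2 | >99% |
| 3 | 25.0% | 15.0 | >99% |

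With 5% in (a), the differences are 1.2, 2.3, 4.5 and 8.6 points.

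**The case against.** **The article is condensed, and the sentence could mean safety assessed by subgroup, PBM against control within each.** This stands in part. The text does not expressly restrict the analysis to the PBM cohort, so the absence of a control group is a reading and not a stated fact. It is still the most literal reading, because the sentence sets (a) against (b) and defines the groups by receipt of optimisation. The confounding is also not a detail left to an analysis plan: the article itself fixes the contrast.

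**Covariate adjustment is foreseen.** The article says that "the Mantel-Haenszel test will be supplemented with a respective multivariate approach accounting for covariates". That provision belongs to the primary test, and its examples are calendar year, concomitant diseases and the asynchrony of study periods. Even if it were extended to urgency, the lack of overlap shown above would defeat it.

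**A reader might infer that the analysis will almost surely favour the optimised patients, even if optimisation is harmful.** The documents do not support this. They give no event rates by urgency and no subgroup sizes. With an assumed urgency odds ratio of 1.25 and 1,000 per group, the chance of a significant difference is only 35%. Equal odds ratios of 1.5 for harm and urgency cancel to 1.00, which is not an apparent benefit. The transfusion-risk restriction, which applies to (a) only, could also push against the expected direction, since (b) may include procedures of lower risk.

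**The consequence is limited.** This stands. It is one secondary subgroup analysis, with no decision rule attached. Neither the primary test nor the monitoring rule uses it.

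**Conclusion.** The point holds as a design flaw in one secondary analysis. Optimisation is fully confounded with urgency and partly with type of procedure, and the contrast as written cannot show whether optimisation or the delay is safe. That conclusion needs only the definitions in the Management and Statistical analysis sections and no assumed number.

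The contrast mixes the two effects, so it would go too far to say that it measures urgency alone. The size and direction of the bias are unknown. The range of about 2 to 15 points rests on three assumptions: no optimisation effect, 10% events in (a), and urgency odds ratios of 1.25 to 3. It should not be set against the 0.5-point non-inferiority margin, which applies to the primary PBM-versus-control test only. That both groups lack a control counterpart is the literal reading, and the authors should confirm or correct it. The primary conclusion is unaffected.

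**What to change.** Replace the a-versus-b contrast with comparisons of PBM against control, using the centre-stratified Mantel-Haenszel method of the primary analysis, within strata defined identically in both cohorts and not by receipt of optimisation:

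- elective surgery on the list of procedures with transfusion risk above 10%;
- urgent or non-elective surgery.

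Report the PBM-versus-control odds ratio with its confidence interval in each stratum, and test the PBM-by-stratum interaction.

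Where a haemoglobin value taken before any PBM treatment exists in both cohorts, restrict each stratum further to anaemic patients. Admission haemoglobin should not serve for this. Elective PBM patients may have been treated before admission, so successfully treated patients could drop out of the anaemic stratum in one cohort only.

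The cost is more than rewording. Urgency, procedure and, if used, haemoglobin must be extracted from the hospital system for both periods, and the Data recording section does not say that they are. The within-stratum comparisons are less precise. They estimate the effect of the whole program in each stratum, because the other two pillars also change between the periods, and not the effect of optimisation alone. The report should say so.

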### Economic evaluation

A cost-utility analysis is being conducted. Resource use data such as blood products transfused, inpatient days by ward type, surgery, medications, complications and their treatment has been integrated into the statistical analysis. The average cost in each group will be calculated, and from this the incremental cost-effectiveness ratio will be derived.

### Clinical study monitoring

An Independent Data Monitoring and Safety Committee will analyse the data on a regular basis. If the implementation of the PBM program will result in a 5% rise of the primary efficacy endpoint compared to the control cohort encompassing all recruited patients from all centers, the IDMC can recommend early termination of the study. Final decision for early termination will be done by the principle investigators.

## Discussion

While transfusion of cellular blood components is a life-saving intervention, over-transfusion can be associated with short and long-term hazards. Therefore risks and benefits of transfusions should be weighed individually in every patient and modifiable risk factors for transfusion such as anaemia should be prevented and treated accordingly [5,9,16,17]. An effective, patient-focused PBM program could help to save a scarce resource and to improve patient outcome and safety [18,19]. In the last ten years, different aspects of a PBM program have been implemented into clinical practice reducing the utilisation of allogeneic red blood cell transfusions and improved outcome [20-24].

Nonetheless, there remains uncertainty about the safety and effectiveness of PBM. Both fear of insufficient tissue oxygenation following a restrictive transfusion trigger and delay of surgery due to preoperative optimisation are the main concerns prevailing.

This study aims to investigate whether or not a PBM program is non-inferior in terms of patient outcome compared to a pre-implementation cohort. The acceptance of the PBM program among physicians will determine the success of this study.

In conclusion, this prospective, multi-centre trial intends to determine whether or not the implementation of a PBM program is safe and effective in about 100.000 hospitalised patients undergoing surgery.

## Trial status and conclusion

This trial is registered at www.clinicaltrials.gov (Identifier: NCT01820949).

The Patient Blood Management program has been implemented in the four university hospitals of Frankfurt, Bonn, Kiel and Muenster.

Despite the complex nature of implementing new clinical standards, this trial has proceeded successfully. The experience and data from this study should help to design and implement fitting PBM programs in other hospitals.

## Abbreviations

IDA: Iron-deficiency anaemia
PBM: Patient Blood Management
RBC: Red blood cells
